# 4. INTERVENTIONS

## 4.1. Description and schedule

In order for the randomization and start of intervention to be as close as possible, CRC will endeavor to randomize the participant immediately after closing for application and send the e-mail about iCBT program course description as soon as possible.

Participants who will be allocated to the intervention group studied the new iCBT program called the Internet CBT program; Useful mental health solutions series for business. The program is a six-week web-based training course to provide stress management skills. This program is structured into six lessons, with one lesson given per week. Learning one lesson required about 30 minutes, including homework. This program can be used anywhere the Internet is available.

One of the unique features of the program is that the training is provided along with a Manga (Japanese comic) story of a psychologist and a client worker to facilitate the understanding of the participants. Several merits of using a comic story and comic characters in education have been acknowledged through research. First, these materials help motivate individuals, and high motivation is useful to keep participants in the program ([Hutchinson, 1949](#_ENREF_16)). Second, they facilitate easy learning. A program with text combined with comic stories would be easier for a learner to understand compared to a text-only program ([Hutchinson, 1949](#_ENREF_16); [Sones, 1944](#_ENREF_32)). Third, comic stories foster learners’ interest in the program ([Sones, 1944](#_ENREF_32)). These merits might be applicable to education in the workplace, because most Japanese people of working age are familiar with comics.

In terms of the CBT components of the program, included are self-monitoring skills, cognitive restructuring skills, assertiveness, problem-solving skills, and relaxation skills. At the end of each lesson, participants are asked to submit homework to facilitate their understanding, although it is voluntary. Participants who will submit their homework will receive feedback from trained staff (clinical psychologists).

Participants will be allowed to complete the six lessons within 10 weeks after the baseline survey. Participants will be reminded by e-mail to complete each lesson if they had not already done so. Reminders will be sent from the research office to the participants every Monday.

The EAP program is the one which has already been in use by this company. The program includes a web site for mental and physical health, a p.r.n. telephone or in-person counseling service accessible to all the employees and on-site lectures on mental and physical health for managers and workers.

Participants in the control group will also receive an e-mail message once a month titled “Useful information for stress management.” Each e-mail message consists of about 500 words in Japanese and included stress management tips. The contents are as follows: 1) How to have a good sleep, 2) The effects of your diet and ingesting alcohol for stress, 3) How to have a good holiday, 4) Relaxing by listening to music and taking a bath, and 5) The effects of exercise on stress.

## 4.2. Quality control of treatments

The iCBT program to be used in this study was developed by the investigators based on cognitive-behavioral theory. The exactly same content will be provided to all participants in the intervention group at each session through a web-based learning management system set up at a server of the Department of Mental Health, University of Tokyo.

Concerning tailored feedback comments for a homework which a respondent submits, the homework will be reviewed and commented on by five psychologists at MSc, PhD or post-PhD level. To ensure a similar quality of the feedback comments, a brief guidance and half-day training will be given to these psychologists face to fade by the CRC ([name]), who is also nan experienced clinical psychologist, with a written manual with several examples. All feedback comments to homeworks will be recorded and reviewed by the CRC to monitor the psychologists’ performance and provide additional training to them if necessary.

## 4.3. Measures of client adherence

The CRC will check for client adherence and send a reminded e-mail to the participant if any of the following is noticed:

1. More than a week have elapsed since the announcement by e-mail about iCBT program
2. More than a week have elapsed between sessions

# 5. ASSESSMENTS

## 5.1. Measures

### Beck Depression Inventory-II (BDI-II)

The Beck Depression Inventory, originally published in 1961 ([A. T. Beck, Ward, Mendelson, Mock, & Erbaugh, 1961](#_ENREF_6)), has been the most widely used self-report measure of depression severity. With the advent of the DSM-IV, the time frame and question items have been updated as the 2nd edition of the BDI, and its reliability and validity have been confirmed ([Aaron T. Beck, Steer, & Brown, 1996](#_ENREF_5)). The reliability and validity of the Japanese version have been found to be excellent ([Hiroe et al., 2005](#_ENREF_14)).

We will administer BDI-II at baseline, at three-month follow-up (end of acute phase treatment) and at six-month follow-up.

### Composite International Diagnostic Interview (CIDI)

The CIDI is a widely used fully-structured diagnostic interview for assessing mental disorders, to be used with the general population by trained lay interviewers ([Robins et al., 1988](#_ENREF_27)). It has been successively updated to accommodate the DSM-IV. We used the most recent computerized version ([Kessler & Ustun, 2004](#_ENREF_24)) and administered the sections for mood disorders. The concordance between the CIDI and standardized clinical assessments has been reported ([Haro et al., 2006](#_ENREF_13)). The Japanese version of the HPQ and CIDI has been used in the World Mental Health Survey in Japan ([Kawakami et al., 2005](#_ENREF_17)).

The face-to-face version of WHO-CIDI 3.0 was translated into Japanese and tested its validity for diagnosing MDE ([Kawakami et al., 2008](#_ENREF_18)).

### Kessler’s psychological distress scale (K6)

K6 is a recently developed very short (6-item) self-report questionnaire to screen for common mental disorders ([Kessler et al., 2002](#_ENREF_21)). It is based on modern item response theory methods and consists of questions that are maximally discriminative of respondents in the 90th-99th percentile range of the general population distribution because it is known that between 5-10% of the population suffer from mental disorders at any point in time. Only items displaying constant psychometric characteristics across sociodemographic variation are included in the final model. K6 has been found to work as well as and better than some widely used screening questionnaires ([Furukawa, Kessler, Slade, & Andrews, 2003](#_ENREF_11); [Kessler, Barker, et al., 2003](#_ENREF_23)). The Japanese version has been validated ([Furukawa et al., 2008](#_ENREF_10)).

We will use K6 as the initial screening instrument. Together with the screening, three-month follow-up and six-month follow-up data (which will all be administered to the control group as well), K6 will be one of the secondary outcome measures.

### Health and Productivity Questionnaire (HPQ)

The World Health Organization health and Productivity Questionnaire (HPQ) is a self-report instrument designed to estimate the workplace costs of health problems in terms of self-reported sickness absence (absenteeism) and reduced job performance (presenteeism). Validation studies have found documented significant associations (r=0.61 to 0.87) of HPQ work hours assessments with payroll records ([Kessler, Barber, et al., 2003](#_ENREF_22)) and job performance assessments with supervisor ratings (r=0.52) ([Kessler et al., 2004](#_ENREF_20)) and other administrative records (area under the curve, 0.58 to 0.72) ([Kessler & Ustun, 2004](#_ENREF_24)).

We will administer HPQ at baseline, at three-month follow-up (end of acute phase treatment) and at six-month follow-up.

### Sick leave days during past 3 month

Respondents will be asked to report the number of Sick leave days during past 3 month.

We will administer the number of Sick leave days during past 3 month at baseline, at three-month follow-up (end of acute phase treatment) and at six-month follow-up.

### Utrecht Work Engagement Scale (UWES)

Work engagement will be assessed using the short form of the Japanese version of the Utrecht Work Engagement Scale (UWES) ([Shimazu et al., 2008](#_ENREF_31)). The UWES consists of 3 subscales comprising 9 items (i.e., vigor, dedication, absorption). Items are scored on a 7-pointscale ranging from 0 (never) to 6 (always). Item examples are “At my job, I feel strong and vigorous” (vigor), “I am enthusiastic about my job” (dedication), and “I am immersed in my work” (absorption). A total score is calculated from all 9 items.

We will administer UWES at baseline, at three-month follow-up (end of acute phase treatment) and at six-month follow-up.

### The 24-item Dysfunctional Attitude Scale (DAS-24)

The 24-item Dysfunctional Attitude Scale (DAS-24) is a short version of the Dysfunctional Attitude Scale, which is a self-report inventory measuring depressogenic schemata. Each item is scored on a scale ranging from one (totally disagree) to seven (totally agree), with a higher score indicating a more dysfunctional attitude ([Power et al., 1994](#_ENREF_25)). The Japanese version has been developed and tested, and its reliability and validity have been established ([Tajima et al., 2007](#_ENREF_34)).

We will administer DAS at baseline, at three-month follow-up (end of acute phase treatment) and at six-month follow-up.

### Improvement of knowledge and self-efficacy

Respondents will be asked to rate their improvement of knowledge and self-efficacy regarding five components of the iCBT program (Stress management, Cognitive restructuring, Assertive communication, Problem-solving, Relaxation training). Knowledge improvement will be assessed by asking participants, “How much knowledge do you have about…” and self-efficacy improvement was assessed by asking respondents “How confident are you that you can do….” Both items were scored on 5-point scale ranging from 0 (none) to 4 (enough).

We will administer the rate of improvement of knowledge and self-efficacy at baseline, at three-month follow-up (end of acute phase treatment) and at six-month follow-up.

## 5.2. Follow-up visit description and schedule

### 5.2.1. Drop out from the intervention

The subject is free to withdraw from the intervention and/or the study at any time. Even if someone discontinues participation in the intervention, we will therefore make every effort to collect outcome data from them at the follow-ups at month three and at month six.

If a new mental condition arises or the existing mental condition worsens, all the participants, whether during the iCBT or outside of the iCBT, are free to utilize the EAP routinely made available by the company and/or seek professional help outside the company. In addition, they can send the e-mail or call up the free hotline connected to the study center psychologist.

If a new mental condition or worsening of the existing subthreshold depression occurs during the iCBT such that treatment outside the current program is advisable, the counselor must advise the subject to seek professional in-person help from the industrial physician, his/her home doctor or a mental health specialist.

The participation in the intervention itself can be continued if the participant see no conflict between the iCBT and the newly offered treatment, or discontinued should there be any perceived conflict or wish to withdraw expressed from the part of the participant. Even if the iCBT itself is discontinued, the participant is encouraged to take part in the three- and six-months follow-ups.

### 5.2.2. Drop out from the study

Those who withdraw consent to the follow-ups at three and/or six months will be considered dropouts from the study.

### 5.2.3. How to enhance adherence and reduce dropouts

Dropout from the intervention will be strictly distinguished and differentiated from dropout from the study. We will ask the client, so far as it is possible with him/her, that he/she respond to the final assessment even if he/she has chosen to stop the iCBT itself.

Non-respondent will receive the reminded e-mail at least two times from the research center during the learning of iCBT and at three- and six-month follow-up surveys.

## 5.3. Assessment of response variables

### 5.3.1. Independence of the self-reports

In this study, all outcomes will be collected on the web-based surveys. CRC can only access the collected data, in order to assure anonymity and independence of the ratings.

### 5.3.2. Data collection

Three-month follow-up (Acute-phase outcomes)

In the intervention group, the primary outcome will be measured at three-month post randomization, i.e. approximately two weeks after the end of the term of learning the iCBT program. In the control group, the endpoint assessment will take place at three-month post randomization.

The outcome data will be collected on the web-based surveys. If no response is received within a week, participants will receive a reminded e-mail asking for completing the web survey. If no response is still available, CRC will send the reminded e-mail to all the participants again.

Six-month follow-up

Both the intervention group and the control group will receive the e-mail which contains information about the URL of research website at six-month post randomization. If no response is received within a week, participants will receive a reminded e-mail asking for completing the web survey. If no response is still available, CRC will send the reminded e-mail to all the participants again.

# 6. ANALYSES

## 6.1. Data analysis

### 6.1.1. Interim monitoring

No interim analysis will be performed.

### 6.1.2. Preliminary Analyses

Our first set of analyses will check for out-of-range values and logical inconsistencies.

We will also compute summary statistics (mean, standard deviation, minimum, maximum, and skewedness) for each of our outcome variables and do a histogram plot to get a graphical picture of the distribution for each outcome. We will do this separately for outcomes at baseline, three- and six-month.

### 6.1.3. Analyses of Baseline Data

For continuous and ordinal variables, such as BD1-II and HPQ, we will compute the means for the control and intervention groups and test whether they are significantly different using a t-test. For all yes/no baseline variables, we will compute the percentage yes in each of the two groups and compare using a 1 degree of freedom chi-square test. We may or may not report the p-values from these tests in our "Table 1", which will compare the groups at baseline. Whether or not we report them will depend on the journal that we submit the main outcome paper to since some journals want them reported and some do not.

### 6.1.4. Analyses of Primary Outcomes

Our two primary outcomes are the BDI-II measure of depression severity and the web-version of the Japanese WHO-CIDI 3.0 measure of the onset of MDE. The BDI-II will be assessed at three- and six-month follow-ups. The Japanese WHO-CIDI 3.0 will be assessed at the six-month follow-up.

The BDI-II is continuous/ordinal variables so will compute the mean score at three- and six-month follow-ups in the two groups, control and intervention. The onset of MDE is discrete variable so will compute the number of incidence at three- and six-month follow-ups in the two groups, control and intervention.

We will first do unadjusted analyses to compare the means using a t-test. We will then do several adjusted analyses. First, ANCOVA or multiple logistic regression analyses will be used to compare the three- and six-month means or the number of incidence on the outcome adjusting for baseline differences on the outcome. We will also do adjusted analyses which control for additional baseline variables, including variables which differ significantly between the control and intervention groups and variables which are strong predictors of the outcome under analysis.

These analyses will be restricted to subjects who complete the three- and six-month follow-ups (all of the statistical methods described above drop from the analysis those with a missing value on the outcome). Since a true intent-to-treat analysis estimates treatment effects based on data from all randomized subjects, not just those who complete a given follow-up, we will also do some mixed-model hierarchical linear models (HLM), using a mixed-model random coefficient model to estimate treatment effects based on all subjects. Subjects are "random effects" with varying intercepts (baseline values) and vary slopes (rates of change from baseline to three- and six-month). The dataset is structured so that each person has up to three records: baseline, three- and six-month follow-ups.

Even subjects who complete only the baseline enter into the analysis and are taken into account when estimating the three- and six-month mean in each group. Such a model can be fit in standard statistical packages such as SPSS, SAS, and STATA.

If conclusions based on the respondent-only and the intent-to-treat analyses are different, we will report intent-to-treat results.

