# 2. OBJECTIVES

## 2.1 Primary question

Our primary question is:

“Among workers with subthreshold depression, will an Internet-based CBT program consisting of cognitive restructuring, assertiveness training, and problem-solving techniques in addition to the standard Employee Assistance Program (EAP) outperform EAP alone, in terms of depression severity (measured with BDI-II) and the onset of major depressive episode (measured with the web-version of the Japanese WHO-CIDI 3.0) at the end of the follow-up survey?”

The primary outcome measures in this study will therefore be:

1. depression severity at three- and six -month post-randomization as measured by the BDI-II
2. the onset of MDE during the 6-month follow-up as measured by the web-version of the Japanese WHO-CIDI 3.0

These two primary outcomes will be used to decide whether or not the intervention was effective.

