### 3.1.2. Exclusion criteria

1. Non-regular or part-time employees.
2. Sick leave for 15 or more days for a physical or mental condition in the past 3 months.
3. Current treatment for a mental health problem from a mental health professional.
4. Having major depressive episode in the past a month, as ascertained by the web-version of the Japanese WHO-CIDI 3.0.
5. Having lifetime history of bipolar disorder, as ascertained by the web-version of the Japanese WHO-CIDI 3.0.

All workers in company A (N=290) and all workers who belonged to three selected departments (N=about 1,500) at the headquarter of company B (the total employee size, c.a. 11,000) will be recruited by an invitation e-mail.

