### 3.3.4. Intervention allocation

We will randomize eligible subjects to intervention and control groups at a ratio of 1:1. Randomization will be stratified on two variables, namely depression severity at baseline (K6=<4 vs. >=5) and center (company A or company B). Assuming that subjects are recruited from 2 sites, there will be a total of 4 strata. The study statistician will prepare 4 lists of random assignments ahead of time, one for each of the 4 strata. Each list will be blocked to ensure that the ratio of intervention to control is exactly 1:1 at set intervals within each stratum. The statistician will send these lists to the research assistant who is not involved in any other aspects of the study and who will build a spreadsheet that enables concealed sequential allocation and will be responsible for keeping these lists in the safe place.

Before randomizing an individual, the CRC will make a final determination of whether or not the person is eligible to be in the randomized trial. For example, prior to randomization, we will exclude those who having major depressive episode in the past a month. Once the CRC determines the eligibility of the participant, she will enter his/her registration number and the stratification variables to the spreadsheet which will automatically generate the allocation according to the pre-determined random sequence. The entered variables cannot be undone in order to guarantee allocation concealment.

Those randomized to control group will be put on a waiting list and after six-month can receive the iCBT if they wish to do so.

One stratification factor is K6>=5 and K6<=4. The cutoff score for K6 selected based on a previous report, which suggested that 4/5 is the optimal cutoff point for K6 in terms of discriminating community residents and patients with mood and anxiety disorders ([Sakurai, Nishi, Kondo, Yanagida, & Kawakami, 2011](#_ENREF_30)).

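### Three parts of the MDE primary analysis do not work as written (the three-month count, the adjustment for baseline MDE and the intent-to-treat model), although a six-month comparison among respondents can still be run

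*Protocol*

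**What the plan says.** Protocol Section 2.1 names two primary outcomes, and both are to decide whether the intervention worked. The second is "the onset of MDE during the 6-month follow-up as measured by the web-version of the Japanese WHO-CIDI 3.0".

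Section 6.1.4 sets the follow-up schedule. For depression severity: "The BDI-II will be assessed at three- and six-month follow-ups". For MDE: "The Japanese WHO-CIDI 3.0 will be assessed at the six-month follow-up". Its next paragraph says: "The onset of MDE is discrete variable so will compute the number of incidence at three- and six-month follow-ups in the two groups".

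The unadjusted comparison is followed by ANCOVA or logistic regression, comparing "the three- and six-month means or the number of incidence on the outcome adjusting for baseline differences on the outcome". Further adjusted models may add other baseline variables. All of these analyses are confined to people who complete the follow-ups.

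To cover all randomised subjects, Section 6.1.4 adds a mixed-model random coefficient analysis. It has subject-specific intercepts and slopes, uses up to three records per person, and estimates the three- and six-month mean in each group. If respondent-only and intent-to-treat conclusions differ, the intent-to-treat result is the one reported.

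On baseline MDE, Section 3.1.2 excludes anyone "Having major depressive episode in the past a month, as ascertained by the web-version of the Japanese WHO-CIDI 3.0". Section 3.3.4 confirms the timing: "prior to randomization, we will exclude those who having major depressive episode in the past a month".

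**The concern.** Each of the three steps fixed for MDE conflicts with something else in the protocol. The three-month count needs a diagnosis that is not scheduled at three months. The baseline adjustment needs a covariate that varies, and eligibility removes all its variation. The intent-to-treat step needs a model that can use people without a six-month CIDI, and the one described cannot do so for a yes/no onset with one follow-up record.

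The third matters most. Section 3.2 expects a quarter of participants not to complete six months. People who are becoming depressed may be among those who stop answering, and Section 6.1.5 on non-response itself warns that bias is more likely if completion differs between arms. For the BDI-II the protocol has an answer to this. For MDE it has a rule giving precedence to an intent-to-treat result, but no workable way to produce one.

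**Working it through.** **The plan's own figures.** The only sample-size calculation (Section 3.2) is in standard deviation units. Two-sided alpha 0.05, 90% power and d = 0.4 give 2 × ((1.960 + 1.282)/0.4)² = 131.3 per arm, against 131 stated. Completion of 75% gives 131 × 0.75 = 98.25, against 98 stated. Both reproduce. No incidence or effect size is given for MDE.

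**(a) Three-month count.**
- Follow-up CIDI scheduled: six months only (Section 6.1.4). The CIDI text in Section 5.1 gives no follow-up schedule.
- Counts planned: three and six months (Section 6.1.4).
- Outcome definition: onset over the six months (Section 2.1).
- CIDI assessments scheduled after baseline and before month six: 0. The three-month count has no stated source.

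**(b) Baseline adjustment.** Past-month MDE is "no" for every randomised person. The logistic design has three columns (intercept, arm, baseline MDE = 0 for all) and rank 2. A trial fit stops with a singular matrix; without the baseline MDE column it runs. If software drops the column automatically, what remains is the unadjusted odds ratio.

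**(c) Intent-to-treat model.** As scheduled, MDE has at most two records per person: a baseline that is always "no" and one at six months.
- The baseline variance is 0 and its covariance with the six-month value is 0. The regression of the six-month value on baseline, through which a baseline-only subject would contribute, is therefore 0/0.
- Only the six-month variance is non-zero, so random intercept, random slope and residual variances cannot be separated.
- The six-month estimate falls back on respondents. With 262 randomised, 262 × 0.25 = 65.5, or about 66 people, are left out.

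**Illustration of what the loss could do (all rates assumed).** Response 80% control and 70% iCBT, averaging the protocol's 75%. Respondent incidence 6% and 3%, so the observed risk ratio is 0.03/0.06 = 0.50.

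| Non-respondent incidence (control, iCBT) | Control, all | iCBT, all | True risk ratio |
|---|---|---|---|
| Twice respondents' in each arm (12%, 6%) | 0.8×0.06 + 0.2×0.12 = 0.072 | 0.7×0.03 + 0.3×0.06 = 0.039 | 0.54 |
| 12% in both arms | 0.072 | 0.7×0.03 + 0.3×0.12 = 0.057 | 0.79 |

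As an outer limit, assume 5 control and 2 iCBT events among 98 respondents per arm, with 131 − 98 = 33 missing per arm. The observed risk difference is (2 − 5)/98 = −0.03. If every missing control and no missing iCBT participant had an onset, it is (2 − 38)/131 = −0.27. In the opposite case it is (35 − 5)/131 = +0.23.

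**Events available for adjustment (assumed rates).** Section 3.3 expects 245 eligible with K6 of 5 or more, so 245 × 0.75/2 is about 92 per arm. With control incidence of 5% to 10% and a risk ratio of 0.5, total events are 92 × (0.05 + 0.025) = 6.9 to 92 × (0.10 + 0.05) = 13.8.

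**The case against.** A reader might infer that MDE cannot be analysed at all. The text does not support that. Section 2.1 needs only onset over six months, the six-month CIDI supplies it, and a logistic regression on arm among respondents can be run. Removing the three-month mention for MDE settles (a).

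A reader might also infer that no adjustment is possible, or that (b) introduces bias. Neither follows. A constant covariate simply drops out, and Section 6.1.4 goes on to allow other baseline variables. What stands is that the adjusted analysis named first for this outcome adjusts for nothing. Lifetime MDE could vary, but it is not the baseline value of this outcome and is not named as the covariate.

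On (a), the six-month CIDI might date onset retrospectively, and Section 5.3.2 speaks of the primary outcome being measured at three months. But the protocol does not say the CIDI will be used that way, and Section 5.3.2 names no instrument.

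On (c), handling of missing binary data is often left to a SAP, and none is at hand. That would answer a mere omission. Here the protocol already fixes the intent-to-treat model and gives its result precedence, without limiting either to the BDI-II. Section 6.1.5 does compare completers with non-completers, but that describes the loss and does not correct for it.

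It is tempting to read the 0.79 as the expected bias. It is not: it assumes no intervention effect among non-respondents, and milder assumptions give 0.54. The 7 to 14 events apply to the K6 ≥ 5 group under assumed rates; the whole-sample analysis in Section 2.3 would have more.

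**Conclusion.** The point holds for three specific steps: the three-month MDE count, the adjustment for baseline MDE, and the intent-to-treat analysis of MDE. It does not extend to the six-month comparison among respondents. Part (a) is a wording conflict and (b) a redundant covariate. Part (c) has the most consequence: a quarter of those randomised are expected to be absent from one of the two primary comparisons, and the rule preferring intent-to-treat results cannot be applied to it.

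These conclusions rest on the protocol's text and its 75% completion figure. The size of any bias does not: the protocol gives no MDE incidence, so the range from 0.54 to 0.79 against an observed 0.50 shows only how far the answer depends on what is assumed about non-respondents. A reader might conclude that a CIDI must be added at three months. The documents do not require it. It would be a new assessment, and Section 3.3.1 describes contact about a current episode only at eligibility.

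**What to change.** 1. In Section 6.1.4, restrict the MDE count to onset over six months from the six-month CIDI, in line with Section 2.1. If a three-month count is wanted, state its data source.
2. Replace the baseline-of-outcome covariate for MDE with a short fixed set already collected: baseline BDI-II and company. Add the K6 stratum only in the whole-sample analysis; among those with K6 of 5 or more it is constant, the same fault as in (b). Use a penalised logistic fit if events are few.
3. State an all-randomised analysis suited to a binary outcome and apply the precedence rule to it. One example is multiple imputation of six-month MDE from arm, baseline variables and three-month BDI-II and K6. Add a sensitivity analysis that varies non-respondents' risk separately by arm.

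The cost is revised wording and a little more analysis, with no new data collection. The limit is that imputation corrects only for loss that the observed scores explain. People who miss both follow-ups have no three-month scores, which is why the sensitivity analysis is needed.
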